### Ethics and dissemination

The study proposal is approved by the Ethics Committee of West China Hospital, Sichuan University (Approval No. 2022–941). Patients will be advised in detail about the purpose, process, possible benefits, and risks of the study. Participation in the study is completely voluntary, and patients can refuse to participate in the study or withdraw from the study at any stage without reason. Their medical treatment and rights and interests will not be affected. All questionnaires, protocols, and results used in the study will be stored in a secure place or with a secure password and will be destroyed within 5 years after the end of the study. No personal patient information will be disclosed in any public report. Every effort will be made to protect the privacy and personal information of the participants’ medical data. This study is focused on health education, and adverse events may include unexpected symptoms or illnesses; whether or not they are related to this study, they will be recorded and reported. Any serious adverse events will be reported immediately to the ethics committee. In case of research-related injury, we will provide free treatment and compensation according to the law. At the end of the study, the follow-up will be terminated when the patients’ blood pressure fluctuated smoothly, and there are no obvious abnormalities in heart rate, electrocardiogram, and sleep for more than 1 month. This study does not involve additional treatment or tests and does not interfere with the patients’ normal treatment. However, when the patient becomes sicker, the study leader will decide to terminate the patient’s participation in order to ensure that the patient receives timely treatment. The findings will be published in a peer-reviewed research journal and presented at conferences in accordance with CONSORT recommendations.

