### Evaluation methods

An assessor-blind method is used; that is, questionnaire collectors are research assistants who are trained in the use of measurement tools but are blinded to the grouping of study subjects. The intervention effects of the three groups of patients will be measured at baseline and 2 months, 3 months, and 6 months after discharge. The evaluation content includes questionnaire surveys and biochemical index measurements. Baseline data (during hospitalization) collection: Patients will complete the assessment at the nurses’ station. Follow-up data (after discharge from the hospital) will be collected as follows: The research assistant will visit the patient at home for data collection. Patients will complete the assessment independently, but those with reading difficulties, visual impairment, or handwriting difficulties will be instructed to complete the questionnaire as each item is read to them in neutral, noncryptic language. After the evaluation, the researchers will check whether the evaluation is complete. If there are missing items, patients will complete the items on the spot and return the evaluation for verification again. Any doubts about the content will be verified with the patient on the spot. Upon completion of data collection at each follow-up time point, each study patient will receive a gift for participating in the study. Basic demographic data will be collected at baseline, including age, sex, ethnicity, education level, marital status, job status, family status, and medical condition.1. Primary outcome (for patients)

The primary outcomes are neurological function status, self-management behavior, quality of life, biochemical indicators, recurrence rate, and unplanned readmission rate.

Neurological status

The National Institutes of Health Stroke Scale (NIHSS) is the most common stroke evaluation index in the world. It covers the anterior and posterior circulation of the brain, including consciousness, movement, sensation, speech, and visual field, with a total of 15 items. NIHSS scores range from 0 to 42, with higher scores indicating more severe neurological impairment [43]. Cai Yefeng et al. introduced the NIHSS in China to conduct a multicenter and large sample test, and the results showed that the Chinese version of the NIHSS had good reliability, validity, and sensitivity [44].

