The Modified Barthel Index (MBI) will be used to assess the patient’s ability to perform ADLs. The scale contains 10 items: eating, grooming (washing face, brushing hair, brushing teeth, shaving), bathing, dressing (unfastening buttons, zipping zippers, putting on shoes and socks), bowel and urine control, toileting, bed-chair transfer, moving on the ground, and walking up and down stairs [45]. Each item is rated on a 1–5 scale as completely dependent, needing a lot of help, needing moderate help, needing little help, and being completely independent. Normal is 100 points, with a score of 91–99 indicating mild dependence; 61–90, moderate dysfunction; 21–60, severe dysfunction; and 0–20 points, completely dependent. The Chinese version has good reliability and validity [46].

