(2) Self-management behavior: The Stroke Self-management Behavior Rating Scale (SSBR) will be used to measure the level of self-management behavior of stroke patients. The scale covers 7 dimensions: disease management, medication management, diet management, daily life management, emotional management, social function and interpersonal management, and rehabilitation exercise management, with a total of 51 items. Each item is scored from 1 to 5 points, and the total score of the scale ranges from 51 to 255. The higher the score, the better the self-management behavior of the patients. The Cronbach’s *α* coefficient is 0.847, and the construct validity is 0.761. The scale has been widely used in China and has good reliability and validity [47].(3) Quality of life: The 12-item Medical Outcomes Study Short Form Health Survey version 2.0 (SF-12 v2) developed by Boston Health Research Institute will be used to measure the quality of life of patients. It has eight dimensions: general health (GH), physical functioning (PF), role physical (RP), bodily pain (BP), vitality (VT), social functioning (SF), role emotional (RE), and mental health (MH), with a total of 12 items. The total score of the GH, PF, RP, and BP dimensions is the physical component summary (PCS). The total score of the SF, RE, MH, and VT dimensions is the mental component summary (MCS), and the standardized score of each part ranges from 0 to 100. The higher the score, the better the quality of life of the patient. The total Cronbach’s *α* coefficient of the Chinese version of the questionnaire is 0.84, and Cronbach’s *α* coefficient of each dimension is greater than 0.70 [48].(4) Recurrence rate: In China, the recurrence rates of stroke patients at 3 months, 6 months, and 1 year are 12.9%, 16.0%, and 17.7%, respectively [49]. The mortality and disability rate after the recurrence of stroke will be higher, which creates a more serious burden for patients and their families. Therefore, the recurrence rate of stroke after discharge will be used as one of the evaluation indicators in this study.(5) Biochemical indicators: Blood glucose and blood pressure are important risk factors for stroke recurrence [50, 51]. In this study, the blood glucose and blood pressure of patients will be measured by a stable glucose meter (Sinocare Anzhun) and an Omron sphygmomanometer (Sinocare BA-802).(6) Unplanned readmissions: Unplanned readmissions for stroke patients are defined as unplanned readmissions to the department of neurology of a hospital for similar conditions within 30 days or less from the date of last discharge to the date of readmission. It is calculated using the following formula [52]: unplanned readmission rate = number of unplanned readmissions/total number of discharges in the group. The Health Commission of China considers unplanned readmission of stroke patients as one of the sensitive indicators of hospital return and an important indicator to evaluate the quality of hospital care [53].

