The SPSS 22.0 statistical analysis software will be used to analyze the data, and *P* < 0.05 (two-sided test) will be considered statistically significant. Count data are described by frequency/constituent ratio, and measurement data are described by mean/standard deviation according to the results of the normality test. Pearson’s chi-square test will be used to compare the count data between groups. One-way analysis of variance will be used to compare the measurement data between the three groups, and the Bonferroni method will be used for further comparison between the two groups. Repeated measures analysis of variance will be used to compare the longitudinal changes in indicators with a normal distribution. If the covariance matrix of the observed values at each time point is symmetric or spherical (Mauchly’s test, *P* ≥ 0.05), no correction will be needed. If the covariance matrix of the observed values at each time point is *P* < 0.05 (Mauchly’s test), the Greenhouse‒Geisser correction test will be used.

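### The rule that ends participation when a patient becomes sicker does not keep outcome assessment going, so later outcomes can be missing because of the outcome itself

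*Protocol article*

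**What the plan says.** Under Ethics and dissemination, the article states that "when the patient becomes sicker, the study leader will decide to terminate the" patient's "participation in order to ensure that the patient receives timely treatment". What ends is participation, not the intervention. The same section says of adverse events that "whether or not they are related to this study, they will be recorded and reported".

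Other parts of the article bear on this:

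- **Abstract (Methods):** the analysis is declared to be intention-to-treat.
- **Participants:** follow-up runs to week 24 after randomisation.
- **Recruitment:** for someone who drops out, the article mentions recording basic information and the reason for leaving. It does not mention later outcomes.
- **Evaluation methods:** effects are "measured at baseline and 2 months, 3 months, and 6 months after discharge". The primary outcomes include neurological status (NIHSS, and "The Modified Barthel Index (MBI) will be used to assess" daily living), self-management, quality of life (SF-12), blood glucose and blood pressure, recurrence, and unplanned readmission. Readmission counts only "within 30 days or less from the date of last discharge to the date of readmission".
- **Data management and statistical analysis:** "Repeated measures analysis of variance will be used to compare the longitudinal changes in indicators with a normal distribution". One-way ANOVA and chi-square tests compare the groups.

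**The concern.** The trigger for leaving the study overlaps with what the study measures. A patient who becomes sicker will tend to have a worse NIHSS, Barthel or SF-12 score, or a recurrent stroke. If such a patient is taken out of the study and not assessed again, the remaining scores are missing because of the patient's outcome. Later comparisons then lean towards patients who did not worsen, rather than describing everyone randomised.

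This cannot be left to an analysis plan. Such a plan can choose how to treat missing values, but it cannot restore assessments that a conduct rule prevented. Nor does the clause's purpose require the loss. Timely treatment is served by stopping the intervention where that is clinically needed, and a later home visit for assessment does not stand in its way.

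**Working it through.** **Reading the sections together.** No stated figure is in dispute, so the main check is textual.

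1. Ethics and dissemination ends participation as a whole, by decision of the study leader, with no threshold.
2. No other section says that the 2-, 3- and 6-month assessments continue after such a decision. The nearest text, in Recruitment, names only basic information and the reason for withdrawal.
3. The Abstract promises intention-to-treat and Participants promises follow-up to week 24. Both need outcomes from patients who worsen.
4. Classical repeated measures ANOVA uses only patients with every visit. Without imputation, one lost visit also removes that patient's earlier scores from that analysis.

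**Scale, using recurrence as the only trigger.** The article gives national "recurrence rates of stroke patients at 3 months, 6 months, and 1 year are 12.9%, 16.0%, and 17.7%, respectively". Applied to 183 patients (61 per arm):

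- 3 months: 0.129 × 183 = 23.6 (7.9 per arm)
- 6 months: 0.160 × 183 = 29.3 (9.8 per arm)

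Let *f* be the share of recurrent patients who are terminated. The document does not give it, so it is an assumption. Patients lacking six-month scores = *f* × 29.3.

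**Power.** One-way ANOVA with 3 groups, α = 0.05, the planned η² = 0.06, noncentrality = 3*n* × 0.06/0.94. At the planned 53 per arm, power is 0.814. Two cases for the remaining *n* per arm:

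- A: ordinary loss has already used the planned allowance (61 to 53), so *n* = 53 × (1 − 0.16*f*).
- B: there is no other loss, so *n* = 61 × (1 − 0.16*f*).

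| *f* (assumed) | Lost of 183 | A: *n* per arm | A: power | B: *n* per arm | B: power |
|---|---|---|---|---|---|
| 0.1 | 2.9 | 52.2 | 0.807 | 60.0 | 0.862 |
| 0.5 | 14.6 | 48.8 | 0.778 | 56.1 | 0.837 |
| 1.0 | 29.3 | 44.5 | 0.736 | 51.2 | 0.799 |

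**Selection, illustration only.** Suppose worsening costs *d* SD on a scale and occurs in 16% of controls and 8% of the intervention arm, with no other effect. The true difference in means is *d* × (0.16 − 0.08): 0.04, 0.08 or 0.12 SD for *d* = 0.5, 1.0 or 1.5. With 12% instead of 8% it is 0.02, 0.04 or 0.06 SD. If every patient who worsens leaves before assessment, those who remain show a difference of 0. Apart from the 16%, which is the article's recurrence rate, these inputs are assumed. They show the mechanism and do not estimate its size in this trial.

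**The case against.** The strongest reply is that this is one safety sentence in a condensed article. The full protocol is said to be available on request and may state what is collected after discontinuation. The sentence does not say that assessment stops, and the intention-to-treat and week-24 statements could be read as showing that it continues. That is fair as to intent. But the article does state a rule, its wording covers participation as a whole, and what it says about drop-outs does not mention later outcomes. If only the intervention was meant, one sentence settles it.

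Several further objections stand as limits on size:

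- The decision is discretionary, so not every worsening leads to termination, and patients who worsen but stay are still assessed.
- Patients terminated after an early visit still contribute to that visit in the one-way ANOVA. The loss of earlier scores applies only to repeated measures ANOVA, and only without imputation.
- A recurrence that triggers termination is probably recorded as an adverse event. The recurrences at risk are those that come after termination.
- Termination after day 30 cannot affect readmission.
- The loss allowance may already be meant to cover terminations. Case A would then count them twice, and case B shows power of 0.80 even if every recurrent patient is terminated.
- The 16.0% is a national rate. It may be lower in the stable patients enrolled here, and it may not run from discharge.

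None of these removes the defect in the rule.

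**Conclusion.** The concern holds, as a cheap improvement. The article fixes a conduct rule that, followed as written, can make later NIHSS, Barthel, SF-12 and recurrence data missing because of the outcome, and this is in tension with its own intention-to-treat statement.

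The size cannot be determined, because no termination rate is given. On the article's recurrence rate, and assuming that 10% to 100% of recurrent patients are terminated, about 3 to 29 of 183 would lack six-month scores. Power would fall from 0.81 to between 0.81 and 0.74 if the loss allowance is already spent, and would be 0.80 or higher if there is no other loss. Power is the lesser issue; the main risk is selection. No direction and no difference between arms is claimed.

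**What to change.** In Ethics and dissemination, say that worsening may stop the intervention on clinical grounds. Add that the 2-, 3- and 6-month outcomes and recurrence, and readmission within its 30-day window, are still collected for every randomised patient to 6 months after discharge, unless the patient withdraws consent to data collection.

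The cost is one or two sentences, plus a few extra home visits or calls for patients who would otherwise have left. The timely-treatment aim is unaffected.

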### Improving adherence to interventions, modifications, and post-trial care

To improve adherence to interventions in each intervention, we repeatedly emphasized the importance of wearing smartwatches to monitor physical signs for patients’ recovery. And the study required patients to upload self-management logs to the cloud platform every other day. The system will have a built-in reminder module to remind patients through WeChat and mobile phone messages. As a reward, patients who upload their reflection logs on time each week will receive a small gift. This study focuses on health education. The medical treatment or rehabilitation methods of patients in the home stage are based on the doctor’s advice, and the study does not involve additional or alternative medical treatment and rehabilitation methods. If the patient has a need during follow-up, the investigator will communicate with the patient’s doctor to provide the patient with a solution to the problem as an alternative treatment or rehabilitation method. After the intervention, the smartwatch will be taken back, but the WeChat group will not be dissolved. Patients can contact the medical staff in the WeChat group for answers if they have any questions.

## Discussion

Most stroke survivors are left with hemiplegia, aphasia, mouth and eye deviations, dysphagia, cognitive impairment, and other functional abnormalities, which require long-term or even lifelong rehabilitation care, which creates a serious burden for patients, families, and society. Studies have shown that the average length of hospital stay for stroke patients is approximately 10 days [68–70]. It is of great significance to obtain continuous, real-time, and precise attention after discharge to promote functional recovery and reduce disability and recurrence rates. However, due to the limitations of medical resources, facilities, equipment, and technology, most real-time and precise management of stroke is limited to patients in the hospital during the acute onset of stroke, and the attention to patients after discharge is often reduced, resulting in a high incidence of adverse outcomes and readmission rates [71]. Therefore, achieving a real-time and precise care model of stroke patients’ self-management during the transition period at a relatively low cost is helpful in improving the overall health service level, which has important clinical significance, academic value, and economic benefits.

This proposed study will evaluate the effectiveness of a resilience improvement intervention program with the help of a wearable device specifically designed for transitional stroke patients. It is an intervention program delivered by trained health professionals in combination with an engineering group. It also provides guidance on self-management behavior for stroke survivors. Due to the lack of previous research on transitional self-management interventions based on wearable devices, under the framework of social ecological theory and resilience theory, we will use SFA to construct a real-time and precise care plan for transitional self-management of stroke patients based on resilience improvement and provide interventions for patients at the individual, relationship, community structure, and culture levels. This model will provide uninterrupted medical services and real-time monitoring for patients. Digital health interventions for patients with wearable devices, on the other hand, require the patient to wear them for a long period of time but may suffer from cost–benefit imbalances and patient uncooperation. This study hopes that by wearing wearable devices for a short period of time, patients can identify problems existing in their own management and individual solutions, so as to form good habits of self-monitoring and self-management. Even if patients are no longer equipped with wearable devices after the intervention, the individualized problem-solving libraries established by the study can also provide directions for patients to maintain high-quality self-management behaviors in the long run.

This study has some limitations. First, the study population is focused on patients with ischemic stroke, and the findings may not be generalizable to patients with hemorrhagic stroke. Second, the main purpose of this study is to improve the self-management ability of patients, that is, patients are required to have a certain degree of self-care ability, so the inclusion criteria required that the BI index be greater than 40, which may have limited the participation of some severely ill patients, and these patients also need our attention. Based on the above limitations, we will extend transition management based on wearable devices to hemorrhagic stroke and critically ill patients in future research. In addition to these limitations, the data collected by the wearable devices used in the study may be inaccurate due to the device or the improper way that patients wore the device. To mitigate these risks, research assistants will repeatedly teach patients and informal caregivers about how to wear and use the device during enrollment, emphasizing the precautions, and allowing patients to practice many times until they become proficient. The wearable device used in this project is a medical-grade smartwatch that can measure blood pressure, heart rate, electrocardiogram, sleep, blood oxygen, exercise status, and other functions. It has been registered as a class II medical device by the China Food and Drug Administration and has good stability and accuracy. At present, research on the “real-time support” care model of stroke patients’ self-management could provide new ideas for breaking through the bottleneck of stroke patients’ insufficient self-management ability. The findings of this work will (1) provide evidence-based information on innovative interventions for patients with stroke during the transition period; (2) offer real-time and precise intervention for patients through wearable technology, stepping out of the original thinking of a single intervention plan, giving patients individualized intervention models based on dynamic patient data, and providing empirical evidence for the application of wearable technology in stroke patients; and (3) stimulate patients’ positive mind set and improve their adaptability in the face of adversity based on resilience theory.

## Trial status

Recruitment had not started when the protocol was submitted. The protocol version is V1, 17 April 2023. The recruitment will begin on May 10, 2023, and will be completed at about April 10, 2024.

## Data Availability

Any data required to support the protocol can be supplied on request. The datasets analyzed during the current study and statistical code are available from the corresponding author upon reasonable request, as is the full protocol. Any important protocol modifications will be communicated with investigators, trial participants, trial registries, journals, and regulators.

